##### Compliance

A controlled feeding trial, as is considered to be the gold standard for evaluating dietary interventions, may enhance the subjects’ adherence to the intervention and decrease confounding dietary habits. At the initial visit, each subsequent visit and during each call with the dietitian, participants will be encouraged to maintain adherence to the study protocol. Any individual issues associated with the diet will also be discussed. Compliance with the study protocol will be evaluated by aforementioned direct interview with child and/or caregiver and analysis of data from the subject diary. The percentage compliance in each group will be calculated by the dietitian. In agreement with other studies, a compliant participant is considered as one who consumes at least 80% of the provided diet [9, 15]. Snacks and meals outside the meal plan will be assessed separately.

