### Assignment of interventions

#### Sequence generation and allocation concealment

Randomization will be based on a computer-generated randomization list developed by an independent investigator with no clinical involvement in the trial. The random numbers will be generated in blocked randomization (using a random block of 4: 2 subjects in group A and 2 in group B) with a 1:1 allocation ratio to ensure good balance between participant characteristics in both groups. The randomization sequence will be created using StatsDirect statistical software. Stratification will not be performed.

Allocation concealment will be ensured using opaque, sealed, numbered envelopes. The data regarding intervention assignments will be stored in a sealed envelope in a safe in the administrative part of the department. An independent person will open the next consecutively number envelope. Information about allocation of each participant will be given to the dietitian. The dietitian will develop a meal plan for each enrolled participant following the allocation. Each meal plan will contain the full name and address of the child. The meal plans will be provided to the catering company. The catering company will not be informed about the type of diet, and no suggestive information will be attached to the all-day box-diet provided to the participant.

After performing the data analysis, code numbers will be opened by the research coordinator (AH). In case any medical problem occurs for which treatment allocation is needed, the code can be broken by a principal researcher (AH, HS).

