#### Blinding

This is a quadruple-blinded trial. In addition to the subjects, the research investigators (AH, HS), outcome assessor (AH), and independent statistician (data analyst) will be blinded until the completion of the data analysis. The participants and their caregivers will be not informed about the characteristics of the diet being consumed (the name and description will not be provided, as in similar previous RCTs [28, 29]). The researcher will encourage the caregivers/participants not to attempt to identify the nature of the provided diet using available data sources; however, an associated bias cannot be excluded. Therefore, after completion of the follow-up period, each participant and outcome assessor will be asked whether he/she believes that active treatment was administered (these data will be published with the final results, as recommended) [15]. The dietitian (AS) will remain unblinded. The procedure was established to maintain separation between the dietitian and outcome assessor and analysts. The primary outcome will be assessed by a blinded researcher (AH). If possible, to increase the similarity of diets in the two groups, low-FODMAP substitutes will be provided in place of high-FODMAP products in the meal plans.

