#### Data analysis

All analyses will be conducted on an intention-to-treat basis, including all patients in the groups to which they are randomized for whom outcomes are available (including dropout and withdrawals). Per-protocol analysis also will be performed, in which all subjects who finish the study according to the protocol will be included.

Descriptive statistics will be used to summarize baseline characteristics. The Student t-test will be used to compare mean values of continuous variables approximating a normal distribution. For non-normally distributed variables, the Mann-Whitney U test will be used. The x^2^ test or Fisher exact test will be used, as appropriate, to compare percentages. The same computer software will be used to calculate the relative risk (RR), number needed to treat (NNT), and mean difference (MD), all with a 95% confidence interval (CI). The difference between study groups will be considered significant when the *p* value is < 0.05, when the 95% CI for RR does not include 1.0, or when 95% CI for MD does not include 0. All statistical tests will be two-tailed and performed at the 5% level of significance.

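### Compliance is a listed secondary outcome, but an unblinded dietitian classifies it from interviews and banded diary data that often cannot settle the 80% cut-off

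*Protocol article*

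**What the plan says.** All references are to the protocol article.

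- **Who calculates compliance.** Compliance section: "The percentage compliance in each group will be calculated by the dietitian".
- **What that person knows.** Sequence generation and allocation concealment: "Information about allocation of each participant will be given to the dietitian". The Blinding section adds that the dietitian "will remain unblinded".
- **What compliance is based on.** Compliance section: "Compliance with the study protocol will be evaluated by aforementioned direct interview with child and/or caregiver and analysis of data from the subject diary". The threshold is that "a compliant participant is considered as one who consumes at least 80% of the provided diet". Snacks and off-plan meals are handled apart from this.
- **What the diary holds.** Under Study procedure and timeline, the child or caregiver records each day how much of each meal was eaten, in three bands: below 50%, 50–79% and 80–100%.
- **Status of the measure.** The Outcomes section lists the percentage of compliant participants among the secondary outcomes.
- **Separation of roles.** Blinding section: "The procedure was established to maintain separation between the dietitian and outcome assessor and analysts". The same section says "The primary outcome will be assessed by a blinded researcher" and makes no such statement for compliance.
- **Per-protocol set.** Data analysis section: "all subjects who finish the study according to the protocol will be included". The only explicit exclusion from this set, under Concomitant care, is the start of a new therapy.
- **Blinded resource already in place.** The independent statistician is blinded until the analysis is complete (Blinding) and receives the de-identified dataset (Access to data).

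**The concern.** For one listed outcome, the person who classifies participants knows their arm, has designed their meals, speaks with them each week and encourages them to adhere. If classification were mechanical this would matter little. It is not mechanical, because the article gives no rule for turning three meal bands into one percentage and none for weighing an interview against the diary. Borderline participants can then be called compliant or not by someone who knows which diet they received, without any intent to favour an arm.

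Two results could be touched. The first is the comparison of compliance between arms, which bears on how feasible and acceptable the low-FODMAP diet is. The second is the per-protocol analysis, if compliance decides who enters it.

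**Working it through.** No figure in the protocol depends on this point, so there is none to reproduce. Two checks apply.

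**1. Can the diary settle the 80% cut-off?**

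Inputs: five meals a day (Diets) for 28 days (Study procedure and timeline), so 5 × 28 = 140 meals; three bands (same section); cut-off 80% (Compliance). Assumption: all meals carry equal weight, which the article does not state.

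Let *a*, *b* and *c* be the shares of meals in the top, middle and lowest band. Then

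- lowest possible intake = 80*a* + 50*b* + 0*c*
- highest possible intake = 100*a* + 79*b* + 49*c*
- midpoint score = 90*a* + 64.5*b* + 24.5*c*

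| Diary pattern | Lowest | Midpoint | Highest | Against 80% |
|---|---|---|---|---|
| all meals top band | 80.0 | 90.0 | 100.0 | compliant |
| 80% top, 20% middle | 74.0 | 84.9 | 95.8 | undecided |
| 60% top, 40% middle | 68.0 | 79.8 | 91.6 | undecided |
| 90% top, 10% lowest | 72.0 | 83.5 | 94.9 | undecided |
| all meals middle band | 50.0 | 64.5 | 79.0 | non-compliant |

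Third row in full: lowest 0.6 × 80 + 0.4 × 50 = 68.0; highest 0.6 × 100 + 0.4 × 79 = 91.6; midpoint 0.6 × 90 + 0.4 × 64.5 = 79.8.

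The uniform diaries classify themselves. The mixed ones do not. The second row is compliant if bands are scored at their midpoints and non-compliant if scored at their lower limits. The third row falls just short at the midpoint and passes at the upper limits. Whoever picks the scoring, or lets the interview decide, decides the class.

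**2. Who makes that choice, and where does it lead?**

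- The Compliance section assigns the calculation to the dietitian. The allocation and Blinding sections leave that person knowing every arm. No section provides a blinded calculation or check.
- Because compliance is a listed secondary outcome, the dietitian acts as the assessor of that outcome. The Blinding section describes the dietitian as kept apart from the outcome assessor and the analysts.
- The Compliance section speaks of compliance with the study protocol, and the per-protocol set takes those who finish according to it. The two can be read together, but the article never says that the 80% rule decides membership.
- The primary outcome is assessed blind and analysed by intention to treat. Compliance does not enter that analysis.

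**The case against.** Several counter-arguments have weight.

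**The unblinded role is declared, and blinded assessment is promised only for the primary outcome.** This is right. The separation sentence concerns persons and does not say that every secondary outcome is assessed blind. The passages are in tension; a reader might infer an outright contradiction, and the text does not go that far.

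**The missing scoring rule is the real source of discretion, whoever calculates.** This is largely right. With a fixed formula the identity of the calculator would matter much less, since the entries come from children or caregivers who are themselves blinded and the cut-off is the same in both arms. But the interview would still be weighed by the unblinded person, so the rule and the reassignment belong together.

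**A diary-only calculation drops a planned source.** This is also right, and the remedy has to say how interview information is used.

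**The per-protocol link is inferred.** A reader might infer that the dietitian decides who enters the per-protocol set. The document does not support this: the only named exclusion is new therapy, and the rule for assigning analysis sets may stand in an analysis plan that is not shown.

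A reader might also be tempted to put a size on the bias. With invented counts of 17/30 against 10/30 responders, the Pearson chi-square test gives p = 0.069. Removing two diet-arm non-responders (17/28) gives 0.037. This does not measure a likely bias. The counts are not in the document. The removal is selected on arm and on response together, and it spares the control arm; removing two control non-responders as well (17/28 against 10/28) gives 0.061. With Fisher's exact test, which the Data analysis section also allows, the two-patient example gives 0.064. It shows only that p-values near 0.05 are fragile at this sample size.

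**Conclusion.** The point holds in a limited form. A listed secondary outcome is classified by a person who knows each allocation, from data that leave mixed diaries undecided at the 80% cut-off. This sits badly with the separation of roles that the protocol describes. The comparison of compliance between arms may be biased. The supportive per-protocol analysis may be biased too, on the unstated condition that finishing according to the protocol includes the 80% rule.

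The intention-to-treat analysis of the primary outcome is untouched. Neither the direction nor the size of any bias can be derived from the document. The intake ranges rest on equal meal weights; other weights would move the limits, but would not by themselves remove the ambiguity of mixed diaries. The change is worth making because the exposure is avoidable with staff and data that the trial already has.

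**What to change.** Change the assignment in the Compliance section as follows.

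1. The dietitian collects the diary and interview data but does not classify participants.
2. The blinded independent statistician classifies each participant from coded diary data, with a formula for the three meal bands that is fixed in advance, including the meal weights.
3. Interview information counts only as entries recorded in the database and under a rule fixed in advance.
4. Any per-protocol exclusion that rests on compliance is made final while the statistician is still blinded. The allocation section already keeps the code closed until after the data analysis, so this step adds little beyond stating it.

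The text should also say whether the 80% rule is a per-protocol criterion.

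Cost: a few hours of the statistician's time and a short change to the text. There is no new visit, data item or member of staff. The downside is that free judgement from the interview, which may sometimes correct a poorly kept diary, is used less.

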##### Follow-up

All study outcomes (see below) will be assessed during the 4 weeks of the intervention. All subjects, after discontinuation or completion of the trial, will be encouraged to continue management of their FAP-NOS or IBS under the care of our department (if feasible, data from responders will be collected prospectively and analyzed, as a part of an independent study) (see Fig. 1).

#### Outcomes

In agreement with recommendations [16], one primary outcome was pre-specified:
**Change in abdominal pain intensity.** Responders will be those with a daily reduction in the intensity of abdominal pain episodes of at least 30% at week 4 compared with baseline, and this value should be at least equal to the Reliable Change Index (RCI) for that sample [16, 27]. A cut-off of 25 mm for RCI change was adopted [16]. This outcome also will be assessed as the change at weeks 1, 2, and 3 from baseline.

For participant timeline, see Table 1.

Secondary outcomes to be assessed during the 4-week intervention, following the standardized core outcome set [17], will be:
**Change in stool consistency.** Responders will be subjects with improvement in their average stool consistency during the last week of the trial compared with baseline [≥1 higher Bristol Stool Scale score in case of IBS-C, or at least one lower score in case of IBS-D] [16]. The change at weeks 1, 2, and 3 from baseline also will be measured.**Change in abdominal pain frequency** at weeks 1, 2, 3, and 4 from baseline [16].**Change in GSRS** [21] **total score** at weeks 1, 2, 3, and 4 from baseline.**Change in KIDSCREEN-10 index** [22] **total score** at weeks 1, 2, 3, and 4 from baseline.**Change in WHO-5** [18] **total score** at weeks 1, 2, 3, and 4 from baseline.**Change in percentage of school attendance** associated with IBS symptoms (at weeks 1, 2, 3, and 4 from baseline).**Change in percentage of parents’ work absenteeism** associated with IBS symptoms in child (at weeks 1, 2, 3, and 4 from baseline).**Change in BMI-for-age z-score**. The BW (kg) and standing height (cm) will be measured following standard methods by an independent nurse at baseline, after 2 weeks, and after 4 weeks. Body Mass Index (BMI) will be calculated using the standard eq. BMI-for-age z-score will be computed using the WHO AnthroPlus software v1.0.4., then assessed and monitored over time using the WHO growth charts by a dietitian.**Percentage of compliant participants** (see Compliance section).**Percentage of tolerability of the low-FODMAP diet.** This outcome will be reported as a mean for each study group, and as a comparison between groups (MD [mean difference] with 95% CI).**Adverse events.** The number of all adverse events and the number of participants reporting adverse events associated with the intervention (with characteristics) will be reported for each study group (see Criteria for discontinuing the intervention and Harms sections).

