#### Eligibility criteria

##### Inclusion criteria

At enrollment, the volunteer children must fulfill all of the following eligibility criteria to be considered for inclusion: (1) age at least 8 years and ≤ 18 years (regardless of race, ethnicity, gender); (2) FAP-NOS or IBS diagnosed according to the Rome IV Criteria [2]; (3) baseline average pain intensity at least 30 mm on a 100-mm Visual Analogue Scale (VAS) [9]; (4) feeding via the oral route; (5) ability to read and comprehend any employed questionnaires/scales; (6) signed informed consent; and (7) stated availability throughout the study period.

Participants with IBS and a stool consistency score > 5 on the Bristol Stool Scale will be classified as having IBS with predominant diarrhea (IBS-D); if the stool consistency score is < 3, the subjects will be classified as having IBS with predominant constipation (IBS-C) [16].

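### The secondary stool-consistency responder rule has no bound, so a child who crosses into the opposite abnormal stool range is counted as improved

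*Protocol article*

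**What the plan says.** The Outcomes section lists change in stool consistency as a secondary outcome. Its general sentence reads: "Responders will be subjects with improvement in their average stool consistency during the last week of the trial compared with baseline". A bracket then makes this operational by subtype, with a minimum shift of one point in each case: "higher Bristol Stool Scale score in case of IBS-C, or at least one lower score in case of IBS-D". The section names no ceiling, floor or target range for the final score. The rule carries a citation to an outside recommendation.

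The cut-offs that define the two subtypes are under Inclusion criteria. A child with IBS and a score above 5 "on the Bristol Stool Scale will be classified as having IBS with predominant diarrhea". For a score below 3, "the subjects will be classified as having IBS with predominant constipation". IBS children scoring 3 to 5 receive neither label, and FAP-NOS children are outside the classification.

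**The concern.** The outcome is meant to capture stools moving away from an abnormal form. The rule as written asks only whether the score moved far enough in one direction. A child who starts constipated and ends with diarrhoea, or the reverse, satisfies it, although the protocol itself would label the final state abnormal. One abnormal state has replaced another, and the child enters the analysis as a success. If this happened more in one arm, that arm's responder proportion, and the relative risk and number needed to treat derived from it, would be flattered by children who had not reached a better state.

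**Working it through.** **Inputs**
- IBS-C response: final minus baseline is at least 1 (Outcomes).
- IBS-D response: baseline minus final is at least 1 (Outcomes).
- Constipation subtype: score below 3. Diarrhoea subtype: score above 5 (Inclusion criteria).
- Assumptions: a Bristol range of 1 to 7, which the documents do not state, and the subtype cut-offs applied to the same averaged score at baseline and in the last week.

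**Step 1. Does every crossing satisfy the rule?** To cross, an average must go from below 3 to above 5, or from above 5 to below 3. In either case the move exceeds 5 − 3 = 2 points. Since 2 is larger than the required 1, every possible crossing is a response. Nothing in the rule removes any of them.

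**Step 2. Examples.**
- Baseline 2 (below 3, IBS-C), final 6: 6 − 2 = 4, at least 1, so a responder. Final 6 is above 5, the diarrhoea range.
- Baseline 6 (above 5, IBS-D), final 2: 6 − 2 = 4, at least 1, so a responder. Final 2 is below 3, the constipation range.

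**Step 3. What the rule admits, in whole scores (illustration).** Qualifying final scores by baseline:

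| Baseline | Subtype | Qualifying finals | Of these, in the opposite range |
|---|---|---|---|
| 1 | IBS-C | 2 to 7 (6) | 6, 7 (2) |
| 2 | IBS-C | 3 to 7 (5) | 6, 7 (2) |
| 6 | IBS-D | 1 to 5 (5) | 1, 2 (2) |
| 7 | IBS-D | 1 to 6 (6) | 1, 2 (2) |

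The total is 6 + 5 + 5 + 6 = 22 qualifying pairs, of which 2 + 2 + 2 + 2 = 8 end in the opposite range. This counts cells on a scale. It gives each pair the same weight, whereas a move from 2 to 3 and one from 2 to 7 are not equally likely, so 8 of 22 is not a probability.

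**Step 4. Effect of a bound.** Barring the opposite range leaves 22 − 8 = 14 pairs: 12 that end between 3 and 5, plus the two partial improvements 1 to 2 and 7 to 6. The bound removes only the crossings and keeps every other response.

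**Step 5. Who can be classified.** From baselines 3, 4 and 5 there are 3 × 7 = 21 pairs, and none meets the rule, because it speaks only of IBS-C and IBS-D. FAP-NOS has no criterion at any score.

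The article states no figure for this outcome that could be reproduced.

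**The case against.** **Improvement already excludes overshoot.** The general sentence speaks of improvement, and a child who ends in the diarrhoea range is not naturally called improved. That is a reasonable reading of intent. But the bracket is the only operational definition, and an analyst applying it would code such a child as a responder. The wording permits the sensible reading without securing it.

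**A crossing would be visible elsewhere.** Bristol scores are recorded weekly, families note health observations, and adverse events are reported by arm. This is true and limits the harm, but it does not alter how the child is coded in this outcome.

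**The rule is cited.** The source is not at hand, so whether it sets a bound cannot be judged. Adopting a cited rule is defensible. It still leaves the rule at odds with the protocol's own cut-offs.

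**Rarity.** A move of more than 2 points in a weekly average is large, and the documents do not suggest that it is common. This stands, and it limits the weight of the point.

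**Stronger readings that the documents do not support.** A reader might infer that a sizeable share of responders would be crossings; the cell counts above cannot show that. A reader might also infer that FAP-NOS children and IBS children scoring 3 to 5 will be counted as non-responders, capping the rate and diluting the contrast. The text does not say so. The rule is expressly conditional on IBS-C or IBS-D, the intention-to-treat statement under Data analysis covers patients with available outcomes, and the abstract says that subtypes are assessed separately. Any dilution figure would rest on an assumed eligible share and assumed response rates. What remains is an unnamed denominator, which merits a clarification.

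**Conclusion.** The point holds for the missing bound. By the article's own cut-offs, a last-week average above 5 in a child with baseline IBS-C, or below 3 in a child with baseline IBS-D, is an abnormal result of the opposite kind, and the stated rule always counts it as improvement. This follows from the text for any averaged score and does not depend on the whole-score illustration.

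Its size in practice cannot be derived: no crossing frequency, baseline stool distribution or subtype share is given, and the number affected may be small. Nor do the documents show that either arm would gain. This is one of eleven secondary outcomes, and the primary pain conclusion is untouched. It is worth correcting because the correction is cheap and uses definitions already in the article, not because a distorted result has been shown.

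**What to change.** Add one condition to the responder definition: a child with baseline IBS-C must have a last-week average not above 5, and a child with baseline IBS-D one not below 3, in addition to the shift of at least one point in the stated direction. Report by arm the number of children who cross into the opposite range.

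As a clarification only, state that the responder proportion is calculated among children with IBS-C or IBS-D at baseline.

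The cost is one or two sentences. The scores are already collected and the cut-offs already defined; visits and sample size do not change. The downside is slightly fewer responders and a small departure from the cited rule. The change should be recorded before the allocation code is opened.

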**Table 1 Tab1:**
[figure not shown]
Participant timeline

Whenever a patient is enrolled, the participant’s case report form (CRF) will be created. Both, the CRF and one copy of the informed consent in paper form will be archived. Data from the CRF will be entered into an electronic database (see Data collection and management section).

Participant will be randomized and allocated to receive the intervention or control diet for 28 days. During the intervention period, the abdominal pain intensity (using the 100-mm VAS score), stool consistency (using the Bristol Stool Form Scale), pain frequency (by reporting the number of episodes/week), school attendance and parents’ work absenteeism (by reporting the number of days of school or work/week missed), and scores on the GSRS, KIDSCREEN-10 index and WHO-5 will be recorded in the subject’s diary each week (see Table 1). For children ≥14 years of age, the study diary will be filled out by themself; for younger children, the diary will be filled out by caregiver. Moreover, the child/caregiver(s) will be reporting the percent of each meal which the subject consumed (< 50%, 50–79% or 80–100%) each day, to estimate the amount of food consumed throughout the trial; the additional snacks consumed also will be reported daily (characteristics and amount). The tolerance of the diet will be assessed each day using a 100-mm VAS and reported in the subject diary. The caregiver and/or participants will be instructed to record in the study diary any observations concerning the health of the child, especially any symptoms which appeared close to a meal. The dietitian will also monitor the subjects’ acceptability of and adherence to the provided diet each week (see Fig. 1).

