#### Methods of additional analyses

Both the primary and secondary outcomes will be analyzed by logistic regression, controlling for three, prespecified, potential confounding variables, i.e., age, sex, and subtype of IBS. The difference between study groups will be considered significant when the *p* value is < 0.05, when the 95% CI for RR (or odds ratio [OR]) does not include 1.0, or when 95% CI for MD does not include 0. All statistical tests will be two-tailed and performed at the 5% level of significance.

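### Six weekly secondary outcomes have no deciding week and only two-sample tests at 5%; a baseline-adjusted repeated-measures model tested at week 4 would be better

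*Protocol article*

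**What the plan says.** The Study procedure and timeline section states that the symptom, quality-of-life and absence measures "will be recorded in the subject’s diary each week". In the Outcomes section, six secondary outcomes are then defined as change "at weeks 1, 2, 3, and 4 from baseline": pain frequency, GSRS total, KIDSCREEN-10, WHO-5, school attendance and parents' work absenteeism. No week is singled out for any of the six.

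Two other weekly outcomes are treated differently. The primary responder outcome is fixed at week 4, with the addition that "This outcome also will be assessed as the change at weeks 1, 2, and 3 from baseline". Stool consistency is a responder outcome for the last week of the trial, with the change at weeks 1-3 measured as well.

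The Data analysis section lists the tests. "The Student t-test will be used to compare mean values of continuous variables approximating a normal distribution", and "For non-normally distributed variables, the Mann-Whitney U test will be used". Percentages go to the chi-square or Fisher exact test. "All statistical tests will be two-tailed and performed at the 5% level of significance". The section on additional analyses says: "Both the primary and secondary outcomes will be analyzed by logistic regression, controlling for three, prespecified, potential confounding variables". The covariates are age, sex and IBS subtype, with no baseline value and no week. The article mentions no longitudinal model, no order among secondary outcomes and no multiplicity adjustment.

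**The concern.** The plan names the tests and the significance rule, so this is an analysis choice that has been made and not a detail left open. For the six outcomes, two things follow.

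First, with four assessment weeks and no deciding one, a significant result in any week can be presented as an effect on that outcome. The article says that the outcomes follow a core outcome set and that the findings are meant to inform guideline groups, so claims on these outcomes are likely to be used.

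Second, a two-sample test on change makes poor use of weekly data. It subtracts the baseline instead of adjusting for it and treats each week on its own. With about 31 evaluable children per arm, the lost precision matters.

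**Working it through.** The plan states neither a number of secondary tests nor a family-wise error rate, so it has no figure of its own to reproduce.

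**Inputs from the article**
- Six outcomes, each at four weeks (Outcomes).
- Two-sided 5% for every test (Data analysis).
- 31 evaluable children per arm (Sample size).

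**Assumed inputs, because the article gives none**
- Correlation between weekly changes of one outcome: 0.5-0.7.
- Correlation between outcomes: 0.2-0.6.
- Correlation of baseline with the later value: 0.3-0.7.

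**Step 1: count.** 6 x 4 = 24 comparisons. With week 4 only, 6.

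**Step 2: expected false positives if the diets do not differ.** This does not depend on the correlations: 24 x 0.05 = 1.2 against 6 x 0.05 = 0.3.

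**Step 3: chance of at least one significant result, tests independent.** This is the upper reference, 1 - 0.95^m:
- m = 24: 1 - 0.95^24 = 70.8%
- m = 6: 1 - 0.95^6 = 26.5%
- m = 4 (one outcome, four weeks): 1 - 0.95^4 = 18.5%

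**Step 4: the same with correlation.** Null trials were simulated with 31 per arm, 6 outcomes x 4 weeks and t-tests at two-sided 5%. Correlation was exchangeable between weeks and between outcomes, and the two were multiplied for different outcomes in different weeks.

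| Setting | 24 tests | 6 week-4 tests | One outcome, 4 weeks |
|---|---|---|---|
| weeks 0.5, outcomes 0.2 | about 62% | about 25% | about 16% |
| weeks 0.7, outcomes 0.6 | about 42% | about 19% | about 13% |

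Over the whole assumed range the results are about 42-62%, 19-26% and 13-16%.

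**Step 5: precision of unadjusted change.** Let baseline and week-4 values have equal variance s^2 and correlation r.
- Variance of change: 2 s^2 (1 - r)
- Variance after adjustment for baseline: s^2 (1 - r^2)
- Ratio: 2(1 - r)/(1 - r^2) = 2/(1 + r)

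This gives 2/1.3 = 1.54 at r = 0.3, 2/1.5 = 1.33 at r = 0.5 and 2/1.7 = 1.18 at r = 0.7.

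**The case against.** **Separate weekly testing is inferred.** The article lists assessment times in one section and generic tests in another. It never says that each week will be tested, and a full analysis plan could set out a longitudinal model. This stands as a caution. Even so, outcomes defined at each of four weeks, together with a list holding only two-sample tests and a blanket 5% rule, most naturally give week-by-week comparisons. The logistic regression does not change that, since it has no term for week.

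**The count can be pushed too far.** A reader might infer 28 or more tests by adding stool consistency at four weeks, and conclude that no weekly outcome has a decisive week. The text does not support this. Stool consistency names the last week, is a binary responder outcome defined for IBS-C and IBS-D, and would go to the chi-square or Fisher test. Its earlier weeks are only said to be measured. Pain intensity names week 4.

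**Missing weeks.** A reader might also infer that a child with a missing week simply drops out of that week's comparison. The Missing data section plans multiple imputation, so this is not a ground for the point.

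**The precision gain comes mainly from baseline adjustment.** With nearly complete data, the week-4 contrast from a flexible repeated-measures model is close to a week-4 comparison adjusted for baseline. That is correct, and Step 5 measures only the baseline part. Weekly two-sample tests are valid; they are less efficient.

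**The simulation is approximate.** The correlations are assumed, and attendance and absence percentages will not behave like normal scores. The figures are therefore ranges.

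**One primary outcome is pre-specified.** Nothing says that the trial can succeed on a secondary outcome. This limits the consequence to how secondary results are read.

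**Conclusion.** The point holds for six secondary outcomes. As stated, the plan gives 24 comparisons at 5% with no deciding week. The chance of at least one false positive among them is about 42-62%, against 19-26% for one week-4 test per outcome. A single outcome carries about 13-16% instead of 5%. Unadjusted change costs about 1.2-1.5 times the variance of a baseline-adjusted comparison. All of these rest on the assumed correlations and on the natural reading that each week is tested.

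The 42-62% must not be read as the trial's risk of a false positive conclusion. The single primary outcome is fixed at week 4 and its type I error is untouched. The change is worth making before unblinding, but it is not a fatal defect.

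**What to change.** - Name week 4 as the test time for each of the six outcomes, in line with the primary outcome.
- For each continuous score, fit one repeated-measures model with baseline value, week, arm and arm x week, and test only the week-4 contrast between arms. For attendance and absence data, use a GEE or a generalised mixed model with the same terms.
- Report weeks 1-3, including those for pain intensity and stool consistency, as estimates with 95% confidence intervals and no significance claims.
- Label the week-4 secondary results as supportive. Six tests at 5% still leave a 19-26% chance of at least one false positive, so the change reduces multiplicity but does not control it.

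The cost is some extra modelling, a covariance structure that has to be chosen in advance, and giving up significance claims for the early weeks. No new data, visits or participants are needed.
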